### Purpose

Using this case-control study design, the study protocol has the following three specific aims and hypotheses,

**Aim 1:** To determine if the total number and specific types of safety tactics and policies are associated with the occurrence of intentional shootings in K-12 public schools.
○ Primary Aim 1 hypothesis—The total number of cumulative safety tactics and policies will be significantly associated with intentional school shootings.○ Secondary Aim 1 hypothesis—When organized into three domains (physical target hardening, emergency response and technologies, and school security), the total number of safety tactics and policies within each domain will be significantly associated with intentional school shootings.**Aim 2:** To determine if the total number and specific types of safety tactics and policies are associated with suspension and expulsion rates in K-12 public schools.
○ Primary Aim 2 hypothesis—The total number of cumulative safety tactics and policies will be significantly associated with student discipline outcomes.○ Secondary Aim 2 hypothesis—When organized into three domains (physical target hardening, emergency response and technologies, and school security), the total number of safety tactics and policies within each domain will be significantly associated with student discipline outcomes.**Aim 3:** To identify if urban/non-urban, economic, and racial disparities modify the relationships between the implementation of safety tactics and policies, suspensions and expulsions, and intentional shootings in K-12 public schools.
○ Aim 3 Hypothesis: Significant urban/non-urban, economic, and racial disparities will modify the relationships between the implementation of safety tactics and policies, suspensions and expulsions, and intentional shootings in K-12 public schools.

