## Methodology

### Sampling frame

National data from a random sample of K-12 public schools around the US are being collected for this case-control study. Case schools are being ascertained through a comprehensive review of multiple national school shooting databases, including the K-12 School Shooting database, the Everytown for Gun Safety database on gunfire on school grounds, and the Washington Post database on school shootings, to identify all schools that have experienced an intentional gunfire against others on the campus during school hours. Control schools will be ascertained via random selection from the US department of Education’s national database on all K-12 schools and matched to case schools in 1:1 ratio. The full set of inclusion and exclusion criteria developed by the study team are included [S1 File].

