#### Case school ascertainment

We are primarily identifying all school shooting cases via the K-12 School Shooting database (SSDB), as these data detail “all incidents in which a gun is fired, or a bullet hits school property for any reason, regardless of the number of victims, time, day of the week” [34]. Two members of the research team have independently coded this list of incidents to identify the cases that meet the proposed study’s criteria for “intentional school shooting.” And a third member of the study team has reviewed any potential discrepancies in coding efforts. By the study’s completion, the list of cases will be a full, national census of schools that have experienced an intentional shooting on school property, during school hours (including one hour prior to official school activities starting and one hour after all official school activities end) beginning January 1, 2015. The study will exclude accidental discharges and attempted suicides where no other person was targeted or shot. It will also exclude any incidents taking place on a school bus or on school property that is non-contiguous with the school’s primary campus. This list of intentional school shootings meeting the study criteria will be cross-referenced via secondary inspection and inclusion of case data from a series of additional databases that also record and publicly report school shooting incidents, including the Washington Post school shooting incident database and the Everytown for Gun Safety list of gunfire on school ground. These databases are being linked and harmonized to detail all school shooting incidents by the definition above, from January 1, 2015 –December 31, 2023.

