#### Control school ascertainment

Control schools are a randomly selected national sample of schools that have not experienced a shooting, by the definition described above and within the same time frame (1/1/2015–12/31/2023). Control schools are being obtained via random selection from a national database of public K-12 schools via the U.S. Department of Education’s National Center for Education Statistics (NCES). For each case school, one control school is being chosen as part of a stratified random sample and matched to each case school based on their geographic state, urban/non-urban status, and elementary/middle/high school status. State and urban/non-urban status will be determined using each school’s address and standard definitions of urbanicity taken from the NCES locale codes.

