**Fig 1 pone.0302622.g001:**
[figure not shown]
Conceptual framework and temporality of the proposed case-control study.

In addition, our research team is exploring whether implementation of school safety tactics and policies prompts the occurrence of school suspensions and expulsions, which may then potentially lead to the occurrence of later school shootings. Some school shooters had been previously expelled or had a history of being suspended. Certain security tactics/policies may increase suspensions/expulsions, which can then affect school shootings. Aim 3 further delineates these potential relationships in terms of urban/non-urban, economic, and racial subgroups. This final aim is key to understanding how various relationships among safety strategies, suspensions/expulsions, and shootings play out for different populations and where school districts and policymakers may best and most effectively focus their safety efforts.

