#### Data analysis plan and study registration

An estimated 658 K-12 public schools will be included in our study sample. The presence or absence (binary 0–1 variables) of each of the 27 safety tactics and policies in case and control schools before each case school’s shooting will be statistically tested as independent variables of interest. The number of safety tactics and policies that each school has in place (from 0–27) will be statistically tested as independent count variables. And the number of suspensions and expulsions that have occurred will also be statistically tested as a proportion of the number of students in each school. Specific safety tactics and policies found to have small numbers will also be combined into groupings of safety tactics and policies as per prior aggregated categories: external target hardening, internal target hardening, student/staff monitoring, emergency procedures/drills, emergency notification technologies, medical support, and school security staff.

Analyses will begin with descriptive statistics to characterize cases and controls relative to independent variables. Categorical and continuous variables will be explored using frequency distributions, means, medians, standard deviations, skewness coefficients, and ranges. Bivariable analyses of predictor variables for each outcome will consist of t -tests, Chi-squared tests, and nonparametric comparison tests. Collinear independent variables will be identified using Spearman coefficients, tolerance statistics, and condition indices. As this population-based case-control study will be matched on state, urban/non-urban, and elementary/middle/high school status, conditional logistic regression model specifications will be used. The first two aims will adjust for confounders that will be methodologically and theoretically justified. The third aim will include interaction analyses with select effect modifiers: urban/nonurban, economic, and racial disparities. Despite having matched on these variables, effect modification analyses with these variables are possible and commonly conducted in case-control studies. Disparities analyses will include adjustments for sparse data. Researchers will reasonably limit the final group of predictor variables to promote statistical efficiency and provide the best unbiased estimators.

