Multiple testing in regression models will be handled by pre-specified variable selection procedures (Benjamini-Hochberg) to control false positive findings in terms of type I error rate and false discovery rate. Several regression models will be tested and compared using Wald statistics, and multiple testing adjustments and false discovery rates accounting for correlated conditions and dependency will also be used to provide appropriate estimates of statistical significance and statistical inference. Our research team has pair-matched to increase efficiency in a situation where the distributions of the matching covariates are drastically different in case and control populations. We will use a double robust, efficient, weighted targeted maximum likelihood procedure for the estimation of causal parameters in matched case-control study designs. Where missing data do exist and are missing at random, researchers will use multiple imputation.

Lastly, in line with best practices regarding data storage and in order to assure research quality and integrity, we will implement processes to maximize the rigor, reproducibility, and generalizability of our proposed study. Openness and transparency are being facilitated by pre-registering our planned methods, analyses, and covariates, and sharing of computer code, datasets, and research results. To reduce the likelihood of any possible publication or confirmation biases that might be skewed towards positive results, primary analyses and hypotheses involving tests of the school tactics and policies specified in our specific aims have been publicly pre-registered via clinicaltrials.gov. We will also take every care to ensure that relevant alternative arguments are considered when presenting our results. This will offer school districts and policymakers at the state and federal levels a sound evidence base for the development of fair, objective, and evidence-based policies.

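### For shootings, the Aim 3 product terms test equal odds ratios; alone they cannot show where safety efforts would prevent most if baseline risk differs between subgroups

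*Protocol article*

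**What the plan says.** Under Purpose, Aim 3 is worded "To identify if urban/non-urban, economic, and racial disparities modify the relationships between the implementation of safety tactics and policies", and its hypothesis is that modification will be found. Neither names a scale. The Study design section, in the text after Fig 1, adds a purpose: the aim is key to how the relationships play out in different populations and to "where school districts and policymakers may best and most effectively focus their safety efforts".

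The analysis is in Data analysis plan and study registration. Because of the matching, "conditional logistic regression model specifications will be used"; for Aim 3, "The third aim will include interaction analyses with select effect modifiers: urban/nonurban, economic, and racial disparities". Later in that section comes a second estimator: "We will use a double robust, efficient, weighted targeted maximum likelihood procedure for the estimation of causal parameters in matched case-control study designs". Its parameter and scale are not named, and it is not linked to Aim 3.

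Controls are "matched to case schools in 1:1 ratio", and each is "matched to each case school based on their geographic state, urban/non-urban status, and elementary/middle/high school status". Of the three modifiers, only urbanicity is in that list. On the case side, "the list of cases will be a full, national census of schools".

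**The concern.** A decision on where to place limited safety resources usually turns on how many schools would be spared a shooting, which is an absolute quantity. A product term in a logistic model compares odds ratios. The two comparisons agree only if the subgroups have the same baseline risk.

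The article gives reason to expect otherwise. It justifies pair-matching by saying that the matching covariates are distributed very differently among cases and controls, and urbanicity is one of them. A factor distributed that differently in shooting and non-shooting schools is a factor on which shooting risk varies. The article does not give the size of the difference or say which stratum has the higher risk.

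At stake is the targeting conclusion. A flat product term could be read as no reason to prioritise any subgroup, although absolute benefit differs several-fold. A significant one could steer attention to the subgroup with the stronger odds ratio, although absolute benefit is equal or larger elsewhere.

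**Working it through.** **Inputs from the article.** 329 cases and 329 controls (Data collection; 2 × 329 = 658, as stated); 1:1 matching; over 90,000 public schools (Introduction); case window 1 January 2015 to 31 December 2023. The crude risk is 329/90,000 = 36.6 per 10,000 schools over nine years.

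**Assumed, because the article gives no figure.** Baseline risk ratio K between the higher- and lower-risk stratum of 2, 3 or 5; exposure prevalence 50%; illustrative odds ratios. For rejection probabilities, 60% of pairs are urban and urban is taken as the higher-risk stratum. For absolute risks, 30% of schools are urban.

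**Step 1: equal odds ratios.** For a rare outcome the risk difference is about baseline risk × (1 − OR), so a common OR gives reductions in the ratio K. With OR 0.6 in both strata and overall risk anchored at 36.6 per 10,000:

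| K | Reduction per 10,000, lower-risk stratum | Reduction per 10,000, higher-risk stratum |
|---|---|---|
| 2 | 14.0 | 28.0 |
| 3 | 11.4 | 34.1 |
| 5 | 8.3 | 41.2 |

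The product term's null is true here, so it rejects about 5% of the time.

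**Step 2: equal risk differences.** Setting the reductions equal gives OR_high = 1 − (1 − OR_low)/K. With OR_low = 0.5, OR_high is 0.75, 0.83 and 0.90.

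In matched pairs with 50% prevalence, half the pairs are discordant. The variance of the log odds ratio is therefore 1/[n × 0.5 × q(1 − q)], with q = OR/(1 + OR).

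- Low stratum: n = 0.4 × 329 = 131.6, q = 1/3, variance 0.0684.
- High stratum at K = 2: n = 197.4, q = 0.429, variance 0.0414.
- Standard error: √0.1098 = 0.331. z = ln(1.5)/0.331 = 1.22.
- Two-sided 5% rejection probability: about 0.23.

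The same formula gives 0.34 at K = 3 and 0.43 at K = 5. Simulation of 20,000 data sets gave 22%, 34% and 42%. With OR_low = 0.6 it gave 14%, 19% and 25%. With 50% or 70% urban pairs and OR_low = 0.5, the range was 19% to 44%.

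**Step 3: opposite ranking.** Take OR 0.5 in the lower-risk and 0.65 in the higher-risk stratum. The odds ratio favours the lower-risk stratum. With the same baseline risks as in Step 1, the reductions are 17.5 against 24.5 per 10,000 (K = 2), 14.3 against 29.8 (K = 3) and 10.4 against 36.1 (K = 5), favouring the other.

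**Step 4: what the conditional model can supply.** Both schools in a pair share urbanicity, so its main effect cancels from the conditional likelihood. The coefficients alone then give no additive contrast for urbanicity. Economic and racial composition are not in the list of matching factors, so their main effects remain, and an additive-interaction measure such as RERI = OR11 − OR10 − OR01 + 1 can be built from them.

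**The case against.** The strongest reply is that nothing here is an error. The formal aim asks whether the relationships are modified, an odds-ratio interaction is a legitimate test of that, and the targeting phrase is rationale, not an estimand. An article may leave the interaction scale to a fuller plan. Most of this stands. The test is valid for its own null, and the point concerns only the targeting use that the article itself announces.

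A reader might infer three stronger things that the documents do not support:

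- **That Aim 3 rests on product terms alone.** The article says the aim will include them, and it plans a weighted targeted maximum likelihood procedure that could deliver absolute effects.
- **That 22% to 42% is inflated type I error.** It is not. The odds ratios truly differ in that scenario, so these are power figures. When the odds ratios are equal the test keeps its 5%.
- **That all of Aim 3 is affected.** Suspensions and expulsions are analysed as proportions of students, so the argument covers the shooting outcome. The inability to form an additive contrast from the conditional model concerns urbanicity alone. The article does speak of having matched on all three modifiers, but its description of control selection does not bear that out.

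Nor does any text say that a non-significant product term will be reported as no modification; that is a risk, not a stated plan.

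**Conclusion.** The point holds in limited form. For the shooting outcome, the interaction model named for Aim 3 answers a ratio-scale question. By itself it does not support a statement about where efforts are most effectively focused, if that means shootings prevented and baseline risks differ. That reading of the purpose is natural but not the only possible one, since relative effectiveness could also be meant.

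The sizes depend on the assumed K, stratum shares, prevalence and odds ratios. The direction needs only K different from 1, which the matching rationale implies for urbanicity; for economic and racial composition it remains an assumption. This is a change that should be made, not a flaw that invalidates Aim 3.

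**What to change.** Keep the conditional logistic interactions and label them as tests on the odds-ratio scale. Rest any targeting statement about shootings on pre-specified subgroup risk differences and their contrast, with 95% confidence intervals. There are two routes:

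1. **Scale subgroup odds ratios by subgroup shooting rates R** (census case counts over schools in the national frame). Raw exposure prevalence in the matched controls should not be used, because controls matched on state and school level do not represent the subgroup's schools. Either reweight controls to the frame, or use the exposure prevalence among cases, pc. For a rare outcome, the risk difference is R × (OR − 1) × [(1 − pc) + pc/OR].
2. **Use the weighted targeted maximum likelihood procedure already planned**, naming the risk difference as its Aim 3 parameter and using case-control weights taken from the same rates.

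For economic and racial composition, RERI from the conditional model is a useful supplement.

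The cost is plan wording and modest analysis. The census and the national frame are already part of the study and data collection is still under way, so this can be fixed in advance. The downside is one more set of Aim 3 estimates with wide intervals. In the simulation with a common odds ratio of 0.5 and prevalence taken as 50%, the additive contrast had power of about 30%, 55% and 75% for K = 2, 3 and 5.

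### Benjamini-Hochberg is labelled a variable selection procedure that controls type I error; it is an FDR adjustment, and selecting tactics with it would risk biased odds ratios

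*Protocol article*

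**What the plan says.** The relevant text is in the protocol article, under Data analysis plan and study registration.

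- **Multiplicity.** Multiple testing is to be "handled by pre-specified variable selection procedures (Benjamini-Hochberg) to control false positive findings in terms of type I error rate and false discovery rate". The next sentence says candidate regression models will be compared by Wald statistics, and that "multiple testing adjustments and false discovery rates accounting for correlated conditions and dependency will also be used". No procedure is named for that second layer.
- **What is tested.** "The presence or absence (binary 0–1 variables) of each of the 27 safety tactics and policies in case and control schools" will be tested, together with the 0 to 27 count. Under Purpose, the primary hypothesis of Aim 1 is that "The total number of cumulative safety tactics and policies will be significantly associated with intentional school shootings". Aim 2 has a parallel hypothesis for discipline outcomes. The secondary hypotheses concern counts within three domains.
- **Model content.** On confounders: "The first two aims will adjust for confounders that will be methodologically and theoretically justified". On predictors: "Researchers will reasonably limit the final group of predictor variables to promote statistical efficiency and provide the best unbiased estimators". The second sentence gives no criterion for the reduction.
- **Estimation.** Conditional logistic regression is specified for the matched design, and in addition: "We will use a double robust, efficient, weighted targeted maximum likelihood procedure for the estimation of causal parameters in matched case-control study designs".

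**The concern.** The multiplicity sentence makes two statements about BH, and neither is right as a general description. BH does not choose model variables: it takes a fixed set of p-values and returns a set of rejections. It controls the expected share of false rejections, whereas a type I error claim over a set of tests is normally read as the chance of any false rejection.

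The label matters because of the text around it. A method called variable selection appears alongside a promise to limit the final predictors and a claim of unbiased estimation. A team following the wording could let BH decide which tactics stay and then report ordinary odds ratios for those only. Estimates that have passed a significance threshold on the same data tend to lie too far from the null, and their intervals cover too seldom. The article intends its results to guide schools and policymakers in choosing individual tactics, so readers would rely on exactly those numbers.

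**Working it through.** **Inputs.** From the article: 27 binary tactics, and 658 schools in 329 matched pairs (329 × 2 = 658, which agrees). The article gives no alpha, q, effect size or correlation between tactics. Assumed here: q = 0.05 two-sided; 5 or 10 real effects among 27; mean z of 2, 3 or 4; tests independent or equally correlated at 0.3.

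**Are these z values plausible?** If exposure is unrelated within pairs and has prevalence p, discordant pairs number about d = 329 × 2p(1 − p), and SE(log OR) ≈ √(4/d).

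- p = 0.2: d = 105.3, SE = 0.195, so z = ln(1.5)/0.195 = 2.08 for an odds ratio of 1.5 and 3.56 for 2.0.
- p = 0.5: d = 164.5, SE = 0.156, so z = 2.60 and 4.45.

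Mean z of 2 to 4 therefore corresponds roughly to odds ratios of 1.5 to 2.

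**Without adjustment.** 1 − 0.95^27 = 0.75 for 27 independent tests, so some adjustment is needed.

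**With BH, all nulls true.** Simulated FDR and family-wise error coincide: 0.051 if independent, 0.046 at correlation 0.3. This is the one case in which the type I claim holds family-wise.

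**With BH, some effects real** (200,000 replicates per row). Inflation is the mean z of selected real effects divided by the true z. Coverage is that of ordinary 95% intervals among all selected tactics.

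| Correlation | Real effects | Mean z | FDR | Family-wise error | Inflation | Coverage, selected |
|---|---|---|---|---|---|---|
| 0 | 5 | 2 | 0.041 | 0.081 | 1.73 | 0.777 |
| 0 | 5 | 3 | 0.041 | 0.158 | 1.21 | 0.905 |
| 0 | 5 | 4 | 0.041 | 0.207 | 1.04 | 0.924 |
| 0 | 10 | 2 | 0.031 | 0.106 | 1.66 | 0.844 |
| 0 | 10 | 3 | 0.031 | 0.228 | 1.16 | 0.929 |
| 0 | 10 | 4 | 0.031 | 0.285 | 1.03 | 0.940 |
| 0.3 | 5 | 2 | 0.038 | 0.079 | 1.71 | 0.764 |
| 0.3 | 5 | 3 | 0.039 | 0.124 | 1.21 | 0.902 |
| 0.3 | 5 | 4 | 0.040 | 0.167 | 1.04 | 0.923 |
| 0.3 | 10 | 2 | 0.030 | 0.099 | 1.63 | 0.841 |
| 0.3 | 10 | 3 | 0.032 | 0.178 | 1.17 | 0.929 |
| 0.3 | 10 | 4 | 0.031 | 0.235 | 1.03 | 0.940 |

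The independent rows agree with theory, where FDR = q × (number of true nulls)/27: 0.05 × 22/27 = 0.041 and 0.05 × 17/27 = 0.031.

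**If all 27 estimates are reported**, coverage is 0.95 in every row. BH changes p-values, not estimates, so the loss arises only from reporting the selected ones.

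**On the odds ratio scale.** Inflation applies to the log odds ratio. At p = 0.2 a true odds ratio of 1.5 (z = 2.08), inflated 1.7-fold, would be reported on average near exp(1.7 × ln 1.5) = 2.0.

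**The case against.** **BH does control type I error in some senses.** BH never rejects a p-value above q, so each single test keeps its own error rate at or below q. It also controls family-wise error when no tactic has any effect. Both points are correct, so a flat statement that BH gives no type I control would be wrong. But per-test control at 5% is what unadjusted testing already gives, and the all-null case is not what the study hypothesises. The promised further adjustments for dependency name no method and do not restore the property.

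**The text does not say BH builds the model.** A reader might infer that significance decides which tactics and confounders stay, and that the reported odds ratios are therefore invalid. The article does not support this. The sentence on limiting predictors does not mention BH. Confounders rest on methodological and theoretical grounds, and the covariates are said to be pre-registered. Nothing says that a model is refitted after selection or that only survivors are reported, and a targeted maximum likelihood estimator is named for the causal parameters. This objection stands, and it makes the bias a conditional risk.

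**The size depends on the scenario.** This is also true. Family-wise error is worst with many strong effects; inflation and under-coverage are worst with few weak ones. They do not peak together.

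**The test families belong in the analysis plan.** This is largely fair. The three domains under Purpose and the seven groupings in the analysis section do differ, but that is a separate matter of definition. The exact families may be set out in an analysis plan not shown here.

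**Conclusion.** The point holds in two parts of different strength.

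1. **Established from the text.** BH is mislabelled as variable selection and credited with a type I error property that it lacks in general. Under the assumptions above, FDR is 0.03 to 0.04 while family-wise error is about 0.08 to 0.29. An unseen analysis plan could add detail, but would not make the published sentence correct.
2. **Conditional.** If BH is used to select, as its label suggests, and unadjusted estimates are given for survivors only, log odds ratios are inflated by about 1.7-fold (z = 2), 1.2-fold (z = 3) or hardly at all (z = 4). Interval coverage is then about 0.76 to 0.94. If every tactic is reported, this harm does not arise.

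The primary hypothesis of each aim concerns a single count, so the point bears mainly on the domain and single-tactic tests. The figures depend on assumed q, effect sizes and correlation, since the article states none.

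**What to change.** - Describe BH as control of the false discovery rate only, and drop the type I error claim for it.
- Test the primary total-count hypothesis of each aim at its own alpha, outside the BH family. Holm across Aims 1 and 2 is optional: the aims have different outcomes, and the article makes no joint claim that requires shared alpha.
- Apply BH to the secondary domain tests and the single-tactic tests.
- State that neither BH nor p-values decide which tactics or confounders stay in a model. Confounders then rest on the theoretical grounds the article already gives.
- Report the estimate and interval for every pre-specified tactic, whatever its p-value, with the BH-adjusted p-value alongside.

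The cost is a change of wording and no new data. Adjusted models become slightly larger, and the stated guarantee for single tactics is weaker than the one now printed, though it is one that BH can deliver.
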